The incidence of the Cervical Radicular Syndrome (CRS) is estimated at 0,8 per 1000 inhabitants (1). This means for the Netherlands approximately 13000 new patients/year. In about 1700 cases an operation is executed (https://[www.kpmg.com/NL/nl/IssuesAndInsights/ArticlesPublications/Documents/PDF/Healthcare/Praktijk](http://www.kpmg.com/NL/nl/IssuesAndInsights/ArticlesPublications/Documents/PDF/Healthcare/Praktijk) variatie-rond-indicatiestelling-in-Nederlandse-ziekenhuizen.pdf). The revised Dutch CRS guideline (2010) states that a CRS existing longer than 2 months which does not respond to conservative treatment, can be indicated for surgical treatment (2). Various surgical approaches for the treatment of cervical disorders causing radiculopathy have been described. Scoville reported the successful removal of cervical discs with a laminectomy in 1944, furthermore, the posterior approach for the treatment of cervical radiculopathy has evolved into keyhole foraminotomy being popularized by Frykholm (3). Cloward, and Smith and Robinson first developed the anterior cervical discectomy approach in 1958 (9,10). Anterior discectomy has become the primary standard for treating cervical degenerative disc diseases resulting in stenosis of the central spinal canal or its neuroforamen. For lateral pathologies such as the foraminal soft disc protrusion or spondylitic stenoses of the neuroforamen, there is still controversy regarding the most adequate surgical approach. The literature in this matter consists of low-quality observational reports (see also systematic review). Both techniques are standard care, but the preference to use one technique above the other is partially based on surgeons’ s preference and not on clear evidence (5,8). The Anterior Cervical Discotomy with Fusion (ACDF) is the dominant option among surgeons in the Netherlands, but 4 arguments are available to challenge this dominance. 1. Morbidity data are in favor of posterior cervical foraminotomy (FOR). 2. Direct costs of FOR appear lower. 3. Indirect costs of FOR appear lower, because it may lead to faster work resumption, however this was analyzed in a suboptimal study design and results may not be generalizable to The Netherlands (9). 4. Clinical outcome for FOR appears non- inferior to ACDF, however this is not based on high quality research. This study proposes to analyze in a high quality design (multiCentre, investigator blinded, randomized controlled trial) the cost-effectiveness of the FOR technique compared to ACDF of 2 large groups of patients treated in a multiCentre setting for cervical monoradiculopathy caused by soft/osteophytic foraminal pathology.

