This study is a nationwide prospective, multiCentre, investigator blinded, randomized controlled trial with long term follow up of 24 months. Blinding of the data, the researcher is mandatory to avoid data interpretation bias. In this trial blinding of the patient or the surgeon is not feasible. Both the FOR (experimental group) and the ACDF(active control) have been established surgical techniques. From the literature, mainly retrospective or prospective cohort studies, it has been shown that both techniques are comparable in terms of clinical effect and complications. However these studies are prone to inclusion (surgeon) bias. Therefore an RCT is mandatory to adequately compare both techniques on efficacy. A non-inferiority trial design is chosen to show whether FOR (experimental) has at least as much efficacy as the ACDF technique (active control) or is worse by an amount less than 10%. It is hypothesized that FOR reduces costs, has fewer complications, leads to less work absenteeism, and leads to higher quality of life. All these parameters are secondary outcome measurements.

This project is a cooperation between the department of neurosurgery UMCG (34 patients/year) and 5 other Dutch neurosurgical departments (Martini Ziekenhuis Groningen (24 patients/year; primary investigator is dr. [name]), Radboud Universitair Medisch Centrum Nijmegen (23 patients/year; primary investigator is prof. dr. [name]), Medisch Spectrum Twente (27/ patients/year; primary investigator is dr. [name]), Atrium/Orbis ziekenhuis (22 patients/year; primary investigator is dr. [name]) and the Medisch Centrum Haaglanden (24 patients/year; primary investigator is dr. [name]). The participating Centres are chosen because of their high volume of spine instrumented surgery and their familiarity with the two surgical procedures. All participating Centres have signed a Letter of Intent. A conservative inclusion ratio of 30% has been chosen so that after one year 154 patients can be included. The total number of patients to include after 2 years will be 308 patients

Study period

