5. Number or percentage of complications in the short (30 days) and long term period (104 weeks) between the two groups
6. Cost-effectiveness (104 weeks)
7. Budget impact (extrapolated to 5 years)
   1. **Randomisation, blinding and treatment allocation**

Enrolment will be performed in the 6 Centres in the Netherlands. Patients are randomized to either FOR or ACDF. Randomization will be executed per patient per Centre by web based block randomization after the informed consent procedure is fulfilled. The Trial Coordination Centre will facilitate the randomization. Number of inclusions per Centre is described in the patient enrolment plan as described in section 6.3 (study procedures).

- 1. **Study procedures**

If the patient seems to be eligible for a surgical procedure, the patient will be invited for a consultation with the neurosurgeon. He/she will inform the patient about the surgical procedure and the possibility to participate in the FACET study. The neurosurgeon will provide the patient with the study-information.

After one week, the patient can let the neurosurgeon know if he/she wants to participate in the study. Subjects who fulfil the inclusion and exclusion criteria and signed the informed consent will proceed to have the surgical procedure. Before the procedure patients will be clinically evaluated by the surgeon and anesthesiologist to be sure the surgical procedure can be performed. Which procedure is decided by randomization. Randomization will take place before the surgical procedure will be performed and after informed consent is signed. The surgeon and the patient will know to which procedure the patient is randomized. The patient will be admitted to the hospital before the procedure and will be monitored by standard hospital practice before and after the procedure. The patient will be discharged from the hospital if he/she is stable according to the responsible physician. Normally a hospital admission for this procedure takes 2-3 days. The patient will be reviewed at the outpatient clinic at 6 weeks after the surgical procedure, which is standard care. At baseline, 6, 26, 52, 78 and 104 weeks after the surgical procedure the patient is invited to fill out a web based self-administered questionnaire to monitor work ability, arm and neck pain, quality of life, complications and costs according to the visit plan (table 1).

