|  | Dec 2016 | Jan 2017 | Feb 2017 | March 2017 | April 2017 | May 2017 | June 2017 | July 2017 | Aug 2017 | Sept 2017 | Oct 2017 | Nov 2017 | Total  enrolment 2 yr |
| UMCG | 3 | 3 | 3 | 3 | 3 | 3 | 3 | 3 | 2 | 2 | 3 | 3 | 34 |
| Martini ziekenhuis | 2 | 2 | 2 | 2 | 2 | 2 | 2 | 2 | 2 | 2 | 2 | 2 | 24 |
| Radboud UMC | 2 | 2 | 2 | 2 | 2 | 2 | 2 | 2 | 2 | 1 | 2 | 2 | 23 |
| Atrium/Orbis  ziekenhuis | 2 | 2 | 2 | 2 | 2 | 2 | 2 | 2 | 1 | 1 | 2 | 2 | 22 |
| MS Twente | 2 | 2 | 2 | 2 | 2 | 2 | 2 | 2 | 2 | 3 | 3 | 3 | 27 |
| MC  Haaglanden | 2 | 2 | 2 | 2 | 2 | 2 | 2 | 2 | 2 | 2 | 2 | 2 | 24 |
|  | | | | | | | | | | | | | 154 |
|  | | | | | | | | | | | | Total | 308 |

- 1. **Withdrawal of individual subjects**

Subjects can leave the study at any time for any reason if they wish to do so without any consequences. The investigator can decide to withdraw a subject from the study for urgent medical reasons.

- - 1. **Replacement of individual subjects after withdrawal**

The goal is to reach 308 patients. When a patient withdraws from the study, he/she will not be replaced since 10% loss of inclusion is calculated within the power calculations of the trial.

- - 1. **Follow-up of subjects withdrawn from treatment**

There will be no follow up of patients who are withdrawn from the study before the surgical procedure has taken place. If patients are withdrawn after they have received the treatment there will be follow up of medical data when necessary without bothering and with permission of the patient. Data of patients after withdrawal will be used and analysed with the intention to treat principle.

- - 1. **Premature termination of the study**

Premature suspension of the study will only occur in specific situations:

- Inclusion ratio: if inclusion one year after the last Centre has included its first patient is in total more than 50% below the amount of patients intended to include in all 6 centres, the study will be terminated.
- Patient health: there are no adverse reactions known on which termination of this study will be mandatory. Both surgical procedures are standard care.

The Medical Ethics committee will be informed about the suspension.

1. **SAFETY REPORTING**
   1. **Section 10 WMO event**

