   1. **Primary study parameter(s)**

Due to the requirements of ZONMW the analyses will be done at 78 weeks, however end of trial analyses will be done at 104 weeks and these data will be published. The primary endpoint (Odom's criteria and self-reported brachialgia) will be analysed as appropriate depending on data distribution with a one sided

0.05 level of significance (non-inferiority). Detailed descriptive statistics will be provided for the data collected and 95% confidence intervals will be calculated for all relevant estimates. Clinical follow-up data will be analysed by analysis of covariance (ANCOVA) or generalized model alternatives for categorical or semi quantitative data. Changes within the treatment groups over time as well as differences between groups will be assessed by intention-to-treat analyses. Also the primary analysis will follow the per protocol principle. Sensitivity analysis will be provided to evaluate robustness of the results with regard to unexpected circumstances (for example, impact of ‘cross-over’ patients who are not treated as randomized but are required to be analysed as randomized and centre effects).

- 1. **Secondary study parameter(s)**

Secondary endpoints will be analysed in an exploratory manner at a two-sided significance level of 5%. Safety and tolerability parameters will be analysed descriptively.

Analysis of time-dependent probabilities of critical events will be performed using the Kaplan-Meier method. Furthermore, multivariate event analyses will be performed using Cox proportional hazard regression models. In addition, for the purpose of a supportive sensitivity analysis, multiple imputation procedures will be applied.

COST-EFFECTIVENESS ANALYSIS

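### Patients withdrawn after open randomisation but before surgery are not followed, so the intention-to-treat comparison can cover all randomised patients only by imputation

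*Combined protocol and SAP*

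**What the plan says.** Under Study procedures: "Randomization will take place before the surgical procedure will be performed and after informed consent is signed". The same section adds: "The surgeon and the patient will know to which procedure the patient is randomized". The Study Design section confirms the point: "In this trial blinding of the patient or the surgeon is not feasible". There is therefore an interval in which a randomised patient knows the arm and has not yet been operated on.

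Under Follow-up of subjects withdrawn from treatment, the rule for that interval is: "There will be no follow up of patients who are withdrawn from the study before the surgical procedure has taken place". Patients withdrawn after surgery get limited follow-up of medical data, with their permission. The paragraph ends: "Data of patients after withdrawal will be used and analysed with the intention to treat principle". The heading speaks of withdrawal from treatment and the text of withdrawal from the study. No sentence distinguishes the two.

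Under Primary study parameter(s), changes within groups and "differences between groups will be assessed by intention-to-treat analyses". The next sentence reads: "Also the primary analysis will follow the per protocol principle". That section also plans a sensitivity analysis for patients not treated as randomised. Multiple imputation appears under Secondary study parameter(s), as a supportive sensitivity analysis with no model stated. Withdrawn patients are not replaced, because the sample size allows for 10% loss. All follow-up questionnaires are timed from surgery.

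**The concern.** A non-inferiority conclusion rests on comparing the groups that randomisation created. Here a patient can learn the allocation, leave before the operation and never contribute an outcome. Arm-related loss is plausible on the protocol's own account: the Introduction calls anterior discectomy with fusion (ACDF) the dominant option in the Netherlands and says that the choice of technique partly reflects surgeon preference.

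If more patients leave one arm, and those who leave would have fared differently from those who stay, the followed groups are no longer comparable. None of the planned safeguards supplies the missing outcomes:

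- The 10% allowance protects power, not comparability.
- The per-protocol analysis omits the same patients, so it is not an independent check.
- The cross-over analysis needs an observed outcome.
- Imputation is supportive only, has no stated model, and is not tied to the primary endpoint.

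Outcomes that were never collected cannot be recovered at the analysis stage.

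**Working it through.** **Inputs from the Sample size calculation and Primary study parameter(s) sections:** success 87% in both arms, margin 10 points, one-sided alpha 0.05, power 0.80, 10% drop-out, 154 per arm. The documents give no pre-surgery withdrawal rate. Every loss count and every success rate among leavers below is an assumption.

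**1. The plan's own figure.** n = (1.645 + 0.842)² × 2 × 0.87 × 0.13 / 0.10² = 139.8, so 140 per arm. 140 × 1.10 = 154, the stated number. (Dividing by 0.90 gives 156.) The stated sample size reproduces.

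**2. Power.** With 154 per arm observed, power is 83.3%. With 10% lost (138.6 per arm), it is 79.7%. Loss within the allowance costs little power, so the issue is bias.

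**3. Bias if followed patients succeed at 87%.** Let k be the excess number of FOR patients lost before surgery and q the success rate they would have had. FOR success is then overstated by k/154 × (0.87 − q):

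- k = 5, q = 0.70: 5/154 × 0.17 = 0.55 points
- k = 10, q = 0.60: 10/154 × 0.27 = 1.75 points
- k = 15, q = 0.50: 15/154 × 0.37 = 3.60 points
- any k, q = 0.87: 0 points

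**4. Effect on the one-sided error.** Set true success over all randomised patients at the margin, 77% for FOR and 87% for ACDF. Let a fraction w of the FOR arm only be lost. Success among followed FOR patients is (0.77 − w × q)/(1 − w). For w = 0.05 and q = 0.50 this is (0.77 − 0.025)/0.95 = 78.4%, an upward shift of 1.4 points. A normal-approximation test with unpooled variance, 154 in ACDF and 154 × (1 − w) in FOR, gives these rates of false non-inferiority (nominal 5%):

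| FOR patients lost | q = 0.50 | q = 0.70 | q = 0.87 |
|---|---|---|---|
| 2% | 6.5% | 5.3% | 4.5% |
| 5% | 9.4% | 5.9% | 3.9% |
| 10% | 17.0% | 7.1% | 2.9% |

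The direction depends on q. Leavers who would do worse than the arm as a whole inflate the error; leavers who would do better reduce it. If both arms lose the same share with the same prognosis, there is little or no bias.

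**The case against.** The follow-up rule covers patients withdrawn from the study. A patient who switches technique and stays in the trial is a cross-over, and the plan analyses that patient as randomised. The closing intention-to-treat sentence follows the one on post-surgery withdrawals and can be read as applying to them alone. The section says who is followed, not who is counted, and a missing outcome does not remove a patient from an intention-to-treat set. Baseline data exist, and multiple imputation and a per-protocol analysis are planned. Patients have a week to decide before consenting, which may limit later withdrawal. A patient who withdraws consent for data cannot be followed under any wording.

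The figures are also open to challenge. An excess of 15 is nearly the whole 10% allowance for one arm (15.4 of 154), which has to last for 104 weeks. A patient who leaves the FOR arm to have ACDF outside the trial might well have about 87% success, which gives no bias, or a conservative one if FOR is truly at the margin.

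Much of this stands. A reader might infer that the rule breaks intention to treat, or that the analysis set is in effect those randomised and operated. The documents define no such set, and the two follow-up sentences do not strictly contradict each other. A reader might also infer that the bias favours FOR, pointing to the 90% to 10% usual-care mix in the Budget Impact Analysis section. That mix is a modelling assumption, and it says nothing about who would leave or how they would fare.

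What the objection does not remove is the gap itself. A patient who declines the allocated operation, leaves, and would still answer questionnaires falls under the no-follow-up rule as written, and no other section provides that patient's outcome.

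**Conclusion.** The point holds as a should-fix. Following the plan as written leaves some randomised patients without outcomes after they know their allocation. A comparison of all randomised patients is then possible only by imputation, for which no model or primary-endpoint role is specified, and the per-protocol analysis cannot serve as a check.

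Size and direction are unknown. Under the assumed 5 to 15 excess FOR losses with 70% to 50% success, FOR success is overstated by about 0.6 to 3.6 points of the 10-point margin. With leavers at 87% success, the bias is zero or conservative. The documents do not support a claim that the primary result would be materially wrong; they support only the claim that the plan leaves it exposed to a loss that is partly avoidable.

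**What to change.** - Replace the no-follow-up sentence with one that separates not having the allocated operation from withdrawing consent for data. Patients in the first group who still consent keep receiving the existing web questionnaires through 104 weeks, timed from randomisation if they are never operated on.
- Define the intention-to-treat set as all randomised patients.
- Report pre-surgery withdrawals, with reasons where given, by arm.
- Add a sensitivity analysis of missing Odom outcomes by arm against the 10% margin. A tipping-point table is one suitable form.

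The cost is a revised protocol sentence, matching consent wording and a few extra questionnaires. The questionnaires are already web based and need no hospital attendance from 26 weeks onward. The required sample size does not change. Patients who withdraw consent for data remain missing and are handled only in the sensitivity analysis. The combined document already carries cost results; if data collection has ended, the analysis-set definition, the by-arm report and the sensitivity analysis can still be done.

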The inclusion of patients starts at December first 2015. Total follow-up is 2 years. At baseline (i.e. at enrolment, before the surgical procedure) and then at 6, 26, 52, 78 and 104 weeks after the surgical procedure patients will fill out questionnaires (see Table 1: Visit plan FACET study). After 78 weeks data the first data analysis will be carried out to proceed in fulfilling the ZonMW end of trial evaluation. ZonMW demands end of trial evaluation within 48 months after start of trial. However, the timeline of inclusion is 24 months and 24 months after surgical procedure patients will be asked to fill out the last questionnaire for final data analysis. Therefore the results of these data (24 months) will be published in an international journal. During these 24 months patients will be followed at different moments in time. For the first 4 visits patients will attend the hospital. For visits 5-8 no visits to the hospital are needed. Only web based questionnaires are to be filled out.

Description of the study visits;

If the patient is eligible for the study, the neurosurgeon will inform the patient orally and in writing. After one week the patient will inform the neurosurgeon whether or not he/she will participate in the study and the inform consent procedure will be fulfilled. Patients who fulfil the inclusion and exclusion criteria and signed the informed consent will be randomized to one of the two surgical procedures. Patients will proceed to have the operation either FOR or ACDF and will be admitted to the hospital one day before or at the day of surgical procedure. The following information will be assessed:

- Visit 1: Baseline evaluation after informed consent is signed
  - Medical and preoperative history
  - Clinical evaluation (signs, symptoms, strength, reflexes)
  - Web based patient self-assessment (questionnaires: arm pain VAS, neck pain VAS, WAI, EQ-5D, NDI, iMCQ, iPCQ)
  - Function X-ray of neck and arm
  - MRI and/or CT (If a patient recently (<6 months before operation) performed a Function X-ray or a MRI and/or CT, the result of these tests could be used as baseline value)
  - Report and record (S)AE (start after randomisation)
- Visit 2: Surgical Procedure (FOR or ACDF)
  - Surgical evaluation report (date, type, antibiotic prophylaxes, level of procedure, instruments, complications and (S)AE’s).
- Visit 3: Day of discharge
  - Clinical evaluation (signs, symptoms, strength, reflexes,)
  - Odom’s criteria)

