The cost-effectiveness analysis will be performed alongside the proposed clinical trial to assess the cost- effectiveness of FOR versus ACDF. There will be two separate outcome measures for the cost- effectiveness analysis, resulting in two incremental cost-effectiveness ratios (ICERs) for FOR as compared to ACDF, the first is incremental costs per extra percentage of patients with arm pain relief, the second is incremental costs per Quality Adjusted Life Year (QALY) gained. The analysis will be performed taking a societal perspective. The time horizon will be equivalent to the full follow-up of the clinical study, which is 24 months. According to pharmaco-economic guidelines (6) discounting will be applied for costs (4%) and effects (1.5%) in the second year. A number of sensitivity analyses will be performed to identify the impact of variables such as the costs of the FOR and ACDF procedures, resource use, and effect size, on cost-effectiveness. A cost-effectiveness acceptability curve will be constructed, based on bootstrap simulations, showing the probability of FOR being cost-effective compared to ACDF at varying levels of the willingness to pay, for either one additional percentage of patients with arm pain relief, or one additional QALY.

PATIENT OUTCOME ANALYSIS

The first outcome for the cost-effectiveness analysis is the percentage of patients with arm pain relief, which will be measured and analysed by the VAS, Odom's criteria, neurological testing and the NDI for the extent of neck pain. The second outcome is QALYs, which are assessed by means of the EQ-5D questionnaire (11) EQ-5D scores will be converted into health state utilities, ranging between 0 and 1, with a higher utility indicating a better health-related Quality of Life (QoL). These utilities will be multiplied with follow-up time spent in that particular health state (area under the curve) to eventually convert into QALYs.

BUDGET IMPACT ANALYSIS (BIA)

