**Table 2. Baseline healthcare resource use and productivity losses.**

|  |  | **Costs in Euro** |  |
| --- | --- | --- | --- |
|  | **Posterior Surgery^a^** | **Anterior Surgery** | **Difference (95% CI)** |
| General practitioner | 85 | 82 | -3 (-30 to 23) |
| Physiotherapist | 141 | 199 | 58 (-18 to 135) |
| Company doctor | 31 | 28 | -3 (-20 to 13) |
| Other primary care^b^ | 35 | 38 | 3 (-35 to 41) |
| Care at home | 0 | 44 | 44 (-10 to 98) |
| Neurosurgeon | 122 | 142 | 20 (-9 to 49) |
| Other outpatient clinic visits | 167 | 134 | -33 (-85 to 19) |
| Pain medication | 33 | 31 | -2 (-18 to 15) |
| Emergency department^c^ | 102 | 25 | -77 (-129 to -25) |
| Hospital admissions | 112 | 90 | -23 (-136 to 91) |
| Additional health care costs^d^ | 80 | 192 | 112 (-4 to 228) |
| **Total health care costs** | **998** | **1,223** | **225 (-141 to 591)** |
| Sick leave before surgery, no, (%)  Sick leave > 85 days, no, (%)  Total days of sick leave | 45 (56)  22 (49)  97 | 55 (61)  20 (36)  110 | 13 (-36 to 63) |
| Absenteeism paid work  *Without friction cost method ^e^*  Absenteeism paid work  *With friction cost method* | 3,154  755 | 4,516  2,161 | 1,362 (-837 to 3,561)  1,405 (483 to 2,328) |
| Presenteeism paid work | 2,542 | 1,927 | -614 (-3,262 to 2,034) |
| Absenteeism unpaid work | 274 | 348 | 74 ( -145 to 294) |
| **Total societal costs^f^** | **3,571** | **4,493** | **922 (-1,944 to 3,788)** |

*Abbreviations: Confidence Interval (CI), Number of patients (no.)*

^a^ Percentages may not total 100, because of rounding. Data was missing for 7 (6%) patients in the posterior group and 7 (6%) in the anterior group. Values are presented as mean costs, expressed in rounded Euros.

^b^ Other primary care includes visits to social workers, occupational therapists, speech therapists, dieticians, alternative therapists and psychologists.

^c^ Emergency department includes visits to the emergency department and transportation to the hospital by ambulance.

^d^ Additional health care costs include daycare or admissions to a health institution other than a hospital, rehabilitation Centre or psychiatric institution.

^e^ The ‘friction cost method’ assumes that after a period of 85 days of complete absence, an employee gets replaced by another worker, and productivity would be restored.

**^f^** Total societal costs include absenteeism with the use of the ‘friction cost method”.

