**Table 3. Cost differentiation with number of patients reporting costs**

|  | **Posterior Surgery**  **n=119** | **Anterior Surgery**  **n=124** | **Difference (95% CI)** |
| --- | --- | --- | --- |
| General practitioner | 634 | 613 | 28 |
| *n reported* | 71 | 78 |  |
| Physiotherapist  *n reported* | 1,179  50 | 1,450  55 | -355 |
| Company doctor | 158 | 182 | -31 |
| *n reported* | 47 | 41 |  |
| Other primary care^b^  *n reported* | 693  30 | 804  28 | -146 |
| Care at home^c^  *n reported* | 886  0 | 1,450  6 | -739 |
| Neurosurgeon  *n reported* | 338  85 | 298  78 | 52 |
| Other outpatient clinic visits  *n reported* | 734  49 | 1,062  47 | -430 |
| Pain medication  *n reported* | 231  51 | 273  49 | -55 |
| Emergency department^d^  *n reported* | 505  15 | 815  15 | -406 |
| Hospital admissions  *n reported* | 1,612  18 | 2,437  24 | -1,082 |
| Additional health care costs^e^  *n reported* | 1,693  40 | 1,991  45 | -391 |
| **Total health care costs** | **12,248** | **16,055** | **-3,807 (-6,580 to -1,127)** |
|  |  |  |  |
| Absenteeism paid work^f^  *n reported* | 8,708  43 | 8,818  40 | -110 |
| Presenteeism paid work^f^  *n reported* | 2,434  25 | 560  18 | 1,874 |
| Absenteeism unpaid work^f^  *n reported* | 4,655  64 | 4,653  53 | 2 |
| **Total productivity losses**  **Total societal costs** | **15,797**  **28,046** | **14,031**  **30,086** | **1,767 (-5,358 to 8,373)**  **-2,674 (-19,603 to 5,547)** |

*Abbreviations: Confidence Interval (CI), Standard deviation (SD), number (n)*

*Values are presented as pooled estimated means in rounded Euros. ‘N reported’ are the number of patients that reported costs for a certain subcategory in the original data set.

^a^ Surgical costs include the price for the procedure, implants and haemostatics, and costs for days of admission to the hospital for the initial intervention.

^b^ Other primary care includes visits to social workers, occupational therapists, speech therapists, dieticians, alternative therapists and psychologists.

^c^ Care at home was not reported by any of the patients in the posterior group, to note is that the reported costs are estimated pooled means, using multiple imputation and bootstrapping.

^d^ Emergency department includes visits to the emergency department and transportation to the hospital by ambulance.

^e^ Additional health care costs include day-care or admissions to a health institution other than a hospital, rehabilitation centre or psychiatric institution.

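### The cost-effectiveness plan specifies no baseline adjustment of incremental QALYs or costs, although baseline EQ-5D and cost questionnaires are collected

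*Combined protocol and SAP*

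**What the plan says.** The economic methods are in the Statistical Analysis section, under Cost-effectiveness analysis and Patient outcome analysis. Two cost-effectiveness ratios are planned. One is cost per extra percentage of patients with arm pain relief; "the second is incremental costs per Quality Adjusted Life Year (QALY) gained". The perspective is societal and the horizon 24 months. QALYs are defined patient by patient: "These utilities will be multiplied with follow-up time spent in that particular health state (area under the curve) to eventually convert into QALYs". Uncertainty is handled by resampling: "A cost-effectiveness acceptability curve will be constructed, based on bootstrap simulations, showing the probability of FOR being cost-effective compared to ACDF". Sensitivity analyses are meant "to identify the impact of variables such as the costs of the FOR and ACDF procedures, resource use, and effect size, on cost-effectiveness".

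None of these sentences says how the arms are to be compared on QALYs or costs, and none names a baseline covariate. The only covariance model in the plan is under Primary study parameter(s): "Clinical follow-up data will be analysed by analysis of covariance (ANCOVA) or generalized model alternatives for categorical or semi quantitative data". Its covariates are not listed, and it is not extended to QALYs or costs.

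The baseline measurements exist. Under Study Design, Visit 1 includes "Web based patient self-assessment (questionnaires: arm pain VAS, neck pain VAS, WAI, EQ-5D, NDI, iMCQ, iPCQ").

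**The concern.** The area under the utility curve starts at the baseline utility, so part of any baseline difference is counted directly. The larger part is indirect: patients with lower utility or higher costs before surgery usually have lower utility or higher costs afterwards. A chance difference between arms at baseline therefore carries into the increments, and baseline information that could narrow the intervals goes unused.

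This matters for the decision the trial is meant to inform. The introduction expects similar arm pain relief and leaves open whether quality of life will differ. If the true QALY difference is small, a chance shift of a few hundredths can set the sign of the cost-per-QALY ratio and move the acceptability curve. The five-year budget impact analysis is also built on these results.

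**Working it through.** **Inputs from the documents.** Questionnaires at baseline and 6, 26, 52, 78 and 104 weeks; effects discounted at 1.5% in year 2; baseline costs in Supplementary Table 2; follow-up costs in Supplementary Table 3. Table 2 prints anterior minus posterior and Table 3 posterior minus anterior, so signs must be aligned. No EQ-5D value, no QALY result and no regression slope is given; those inputs are assumptions below.

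**1. Printed baseline differences.** Friction-method absenteeism: 2,161 - 755 = 1,406, printed as "1,405 (483 to 2,328"). SE = (2,328 - 483)/(2 x 1.96) = 471, p about 0.003. Emergency department: 25 - 102 = -77 (-129 to -25), SE 26.5, p about 0.004. These are the only two of the table's 18 intervals that exclude zero. Both totals include it: health care 225 (-141 to 591), p about 0.23; societal 922 (-1,944 to 3,788), p about 0.53.

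**2. Effect of adjustment on costs.** Adjusted difference = unadjusted difference - b x (baseline posterior - baseline anterior), with b the assumed slope of follow-up cost on baseline cost.

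- Absenteeism: follow-up 8,708 - 8,818 = -110 and baseline 755 - 2,161 = -1,406. Adjusted = -110 + 1,406b. It is zero at b = 110/1,406 = 0.08 and +593 at b = 0.5.
- Total health care: -3,807 + 225b. At b = 1 it is -3,582; it reaches zero only at b of about 17.
- Total societal: from the printed -2,674, adding 922b gives -1,752 at b = 1 and zero at b of about 2.9. From the subtracted means, 28,046 - 30,086 = -2,040, it gives -1,118 at b = 1 and zero at b of about 2.2.

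The health care result is therefore robust to adjustment, and the sensitivity lies mainly in the planned societal perspective. The societal lines are rough, because the posterior baseline societal total (3,571) equals its productivity items alone (755 + 2,542 + 274).

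**3. Effect on QALYs.** By the trapezoid rule the baseline utility has weight (6/2)/52 = 0.058 year. The remaining weight, with year 2 discounted, is (1 - 0.058) + 1/1.015 = 1.927 years. For a baseline imbalance d and an assumed slope s of later on baseline utility, shift = d x (0.058 + 1.927s).

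- d = 0.02, s = 0.4: 0.02 x 0.829 = 0.017 QALY.
- d = 0.05, s = 0.6: 0.05 x 1.214 = 0.061 QALY.

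For d = 0.05 the outer limits are 0.003 QALY (only the baseline point carries the imbalance) and 0.099 QALY (it persists in full for 24 months).

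**4. Precision.** The ratio of adjusted to unadjusted interval width is about sqrt(1 - r^2), with r the correlation of baseline with outcome: 0.95 at r = 0.3, 0.87 at r = 0.5 and 0.80 at r = 0.6. Intervals are thus about 5 to 20% narrower over this assumed range.

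**The case against.** Randomisation in blocks within centre makes the unadjusted contrast unbiased on average, so there is no systematic error to correct. That stands. The issue is chance imbalance and lost precision. Two limits apply to the defence. Unbiasedness on average does not remove an imbalance that has occurred. Also, the planes against Odom success use only patients with complete cost data and an Odom score: 80 + 73 = 153 of the 119 + 124 = 243 in Table 3, or 63%. That group is selected after randomisation, so its balance is not guaranteed.

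The plan is silent rather than explicit. A reader might infer that the increments are raw arm differences and that Table 3 confirms it. The documents do not support this. The QALY sentence describes one patient's QALYs, not the arm comparison. Only 5 of the 17 printed differences in Table 3 equal the subtracted means; the 11 health care component rows and the societal total do not (hospital admissions: -825 by subtraction, -1,082 printed). Agreement would prove nothing anyway, since covariate-adjusted means also subtract to the adjusted difference.

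A reader might also set the baseline absenteeism gap of EUR 1,405 beside the follow-up productivity difference of EUR 1,767. That fails. On one sign convention they are -1,405 and +1,767, and the latter is almost all presenteeism (1,874), while absenteeism contributes -110.

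Finally, Table 2 is a results table that could not have informed the plan. This also stands, but the omission does not depend on it: both baselines were scheduled from the start.

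**Conclusion.** The point holds as an omission with a better method freely available. The plan specifies no baseline adjustment of incremental QALYs or costs, and its ANCOVA is confined to clinical follow-up data, although the needed baselines are collected.

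The QALY size rests wholly on assumptions: about 0.02 to 0.06 QALY over two years for an imbalance of 0.02 to 0.05 and a slope of 0.4 to 0.6. The same applies to the gain in precision. For costs, imbalance is visible in two components that point in opposite directions, not in either total. The absenteeism difference would change sign at a slope of only 0.08; the health care difference would barely move.

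It would go too far to say that the arms differed at baseline overall, that utilities were imbalanced, or that the published increments are biased. Table 2 contains no EQ-5D, and the documents do not show which estimator was used.

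**What to change.** State the estimator in the cost-effectiveness section. Within each imputed and bootstrap data set:

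- regress QALYs on arm, baseline EQ-5D utility and centre;
- regress costs on arm, baseline costs and centre, using the same resample so that the correlation between costs and effects is kept;
- take the adjusted increments into the cost-effectiveness ratios, the planes and the acceptability curve;
- show the unadjusted increments as a sensitivity analysis.

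Table 2 reports missing data for 7 patients per arm; missing baseline values can go into the same imputation model. If the adjusted analysis is added now that results are known, label it so and show both versions side by side.

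The cost is a few lines of text and a modest change to the analysis code, with no new data and no burden on patients.

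Separately, reconcile Table 3. The health care component rows and the societal total are printed at about 1.31 times the subtracted means, without explanation. A near-constant factor does not look like row-by-row baseline adjustment.
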